## Abstract

**Background:**

Diabetes distress (DD), a type of psychological distress specific to people with diabetes, is strongly associated with difficulties in performing self-care and inability to meet glycemic targets. Despite increased recognition of the need to manage DD, interventions that are both feasible and effective for reducing DD in routine care settings are not yet known. A pilot study showed that health coaching (HC) has some efficacy in addressing DD, but no adequately powered study has implemented a pragmatic research design capable of assessing the real-world effectiveness of HC in reducing DD.

**Objective:**

The aim of this study is to describe the rationale and design of an ongoing clinical trial, Coaching and Education for Diabetes Distress trial, that seeks to assess whether HC effectively reduces DD among primary care patients with diabetes and whether HC is more effective than an educational program targeting DD.

**Methods:**

The 2-arm randomized controlled trial is taking place at an academic family medicine practice in Houston, Texas. Both arms will receive usual care, which includes education about DD. In addition, the intervention arm will receive 8 HC sessions over a 5-month period. The primary outcome measure is reduction in DD over a 6-month period. Additional outcome measures include changes in hemoglobin A_1c_ and self-care practices (medication-taking, dietary, and physical activity behaviors).

**Results:**

As of March 2019, screening and recruitment are ongoing, and the results are expected by July 2020.

**Conclusions:**

HC is feasible in primary care and has been successfully applied to improving chronic disease self-management and outcomes. This study will provide evidence as to whether it has significant value in addressing important unmet psychological and behavioral needs of patients with diabetes.

**Trial Registration:**

ClinicalTrials.gov NCT03617146; https://clinicaltrials.gov/ct2/show/NCT03617146 (Archived by WebCite at http://www.webcitation.org/76Va37dbO)

**International Registered Report Identifier (IRRID):**

DERR1-10.2196/12166

## Introduction

Diabetes distress (DD) is a negative emotional reaction to diagnosis of diabetes and concerns about treatment demands, risk of complications, and inadequate support [1]. DD, along with major depressive disorder (MDD) and other depressive symptomatology, constitutes significant emotional and psychological burden to people with diabetes [1,2]. Among these distinct conditions, DD is most strongly associated with difficulties in performing self-care and inability to meet glycemic targets [2-4], and it is more common than MDD [5], leading to calls for DD management to become an essential component of diabetes care [1,6].

A review by Sturt et al [7] identified 6 approaches to address types of DD that have been studied; namely, *psychological* (eg, psychotherapy), *educational* (purely informational), *educational with some behavioral component*, *psychoeducational* (education plus a psychological intervention targeting motivation or affect), *medications and devices*, and *care management or case management* [7]. Of these, psychoeducational approaches were the only approaches found to significantly reduce DD compared with controls. Similarly, a subsequent review [8] found that DD showed improvement following interventions that target both emotion (motivational strategies) and cognition (enlightenment or education).

Psychoeducational interventions that target emotion and cognition are a broad category that includes strategies such as health coaching (HC) and psychotherapy plus education; therefore, it is necessary to identify emotion-cognition interventions that are both feasible and effective for reducing DD in routine care settings. HC is an evolving profession that helps individuals achieve sustainable behavioral change through a growth-promoting relationship that elicits autonomous motivation and improves knowledge, self-efficacy, and self-regulation [9]. HC is particularly important to diabetes care as it has the potential to address both DD and self-care.

The American Diabetes Association (ADA) recommends that providers “routinely monitor people with diabetes for DD, particularly when treatment targets are not met...” [10]. However, ADA’s recommendations for dealing with DD (ie, education, referral to a behavioral health provider, or referral to a mental health specialist) are varied and confusing [10]. On the other hand, the Canadian Diabetes Association [11] recommends an approach that is consistent with HC as defined by Olsen [12] and Wolever et al [13]. Even though some interventions have incorporated elements of coaching [7,8], only 1 study has explicitly sought to address DD as a primary outcome using HC [14]. This study found HC to be effective in addressing DD, but the finding has limited generalizability because of methodological limitations such as a small sample size and restriction to a single gender [14]. A recent trial that combined diabetes self-management education with some elements of HC and additional support was successful in addressing DD, but the intervention was too intensive to be feasible and scalable in routine primary care [15]. We proposed to conduct a randomized controlled trial (RCT) to fill the void in the available evidence on the real-world effectiveness of HC on DD. The primary aims of the study are to assess whether education alone is sufficient to address DD and whether HC has additional benefits in addressing DD beyond the effects of education. As coaching services are not typically reimbursed by insurance, cost has been a barrier to greater integration of HC in chronic illness care [16]. Therefore, one of the secondary aims of the study is to assess the willingness of patients with DD to pay for HC. The other secondary aim is to find out whether HC has additional impact on diabetes self-care and hemoglobin A_1c_ (HbA_1c_), beyond any effects observed in the group that receives only an educational program targeting DD.

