## Methods

### Study Design and Setting

A 2-arm, parallel RCT is being conducted among adults with diabetes who are not meeting glycemic targets (defined as HbA_1c_ ≥8.0), at an academic family medicine clinic in Houston, Texas. The overarching goal of the study is to use a pragmatic approach to assess the effectiveness of HC in addressing DD in real-world primary care settings, in which most diabetes care is coordinated and monitored. Therefore, participants randomized to the control group will receive the current standard of care for patients not meeting glycemic targets at the study clinic as summarized in Textbox 1.

Both arms of the study (control and intervention) will receive the standard of care detailed in Textbox 1. In addition, the intervention arm will receive 8 HC sessions to address DD. The HC sessions will be held biweekly in the first 3 months (6 sessions), followed by monthly sessions in the fourth and fifth month.

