Standard of care for diabetes at the study site.Quarterly follow-up visits during which patients receive ongoing, comprehensive assessment and treatment. When patients with diabetes whose HbA_1c_ is 8.0 or above exceed a 4-month period without a visit, they are contacted to schedule a follow-up appointment.Pharmacologic treatment of diabetes and comorbiditiesBehavioral management—diabetes self-management education and support (DSMES), that covers lifestyle modification counseling (nutrition and physical activity), medication-taking behaviors, foot care, how to monitor blood glucose (especially for those on insulin), and how to administer insulin if on insulin. This ongoing DSMES is provided through different means as follows:Directly by primary care providersVia health education handouts in the form of printed materials and via an electronic patient portalBy referral to a registered dietitian located at the clinicReferral to an ophthalmology clinic for annual eye check-upPsychological management—as part of a newly developed quality improvement project, and in line with the 2018 American Diabetes Association’s Standards of Medical Care in Diabetes [10], the clinic has implemented psychological screening (depression and diabetes distress) for patients not meeting their glycemic targets (defined as HbA_1c_ ≥8.0). The plan of action is as follows:Patients who screen positive for depression (using the Patient Health Questionnaire) [17] will be referred to colocated mental health providers.A diabetes distress (DD)-specific education program has been developed for patients with DD and is being piloted through this study (Multimedia Appendix 1). This education program is oriented around the 4 domains of DD—regimen distress, emotional burden, interpersonal distress, and physician distress. Patients are provided feedback on DD screening results and are advised on ways to deal with the areas of greatest distress. Screening for DD is done using the 17-item DD scale (DDS17) [18].

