### Training of Intervention Staff

HC will be provided by a registered dietitian trained and certified as a Health and Wellness Coach by one of the “Transition Programs” approved by the International Consortium for Health and Wellness Coaching [31]. The International Consortium for Health and Wellness Coaching is an organization working to standardize HC practice in the United States and across the world. DD-specific education (Multimedia Appendix 1) for participants in both arms of the study will be provided by designated medical assistants in the clinic who were trained to provide this education in a consistent manner (Textbox 1).

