Inclusion and exclusion criteria for the Coaching and Education for Diabetes Distress trial.Inclusion criteriaHas had a diagnosis of type 2 diabetes for at least 6 monthsAged 18 to 75 yearsMost recent hemoglobin A_1c_ taken within 30 days was 8.0 or aboveAt least a moderate diabetes distress, operationalized as a mean score of 2.0 or more on the 17-item diabetes distress scale [32]Exclusion criteriaModerately-severe to severe depression: Patient health questionnaire-9 score 15 or above [17]Other severe mental health disorder (eg, Alzheimer’s or schizophrenia)Current pregnancySevere diabetes complications or functional deficits (eg, kidney failure requiring dialysis, amputation, or blindness)

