### Measures and Data Collection

The variables that will be measured and the timeframe for data collection are summarized in Table 2. The primary outcome measure will be short-term (6 months) changes in DD score. Secondary outcome measures of interest are willingness-to-pay (WTP) for and satisfaction with HC, as well as changes in HbA_1c_ and diabetes self-care practices, specifically dietary intake, physical activity, and medication-taking behaviors.

DD, self-care behaviors, and HbA_1c_ will be assessed at 3 measurement periods, at baseline (randomization), and at the third and sixth month postrandomization. DD will be assessed using the previously validated 17-item DDS [18]. HbA_1c_ will be tested at every 3-month follow-up visit as part of usual care for patients not meeting glucose targets. Self-care practices (diet, physical activity, and medication-taking behaviors) will be assessed with the respective subscales of the Summary of Diabetes Self-Care Activities questionnaire [30]. Satisfaction with HC will be assessed for the intervention arm at the end of the study (sixth month) through self-administered surveys, including Likert scale-type questions and open-ended questions. WTP for HC will be assessed through an indirect survey approach, which has been shown to be preferable because of higher internal and external validity compared with other methods [34]. In such indirect approaches, participants are confronted with different attribute combinations of various products or services (eg, HC vs alternative interventions) with assigned prices, and they choose the most preferred scenarios. Specifically, we will conduct a discrete choice experiment to assess WTP.

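### The primary aim on education alone has no comparator: both arms receive the education, so the control arm's change cannot show whether it works

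*Protocol article*

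**What the plan says.** The Introduction lists two primary aims. The first is "The primary aims of the study are to assess whether education alone is sufficient to address DD"; the second is whether coaching adds benefit beyond education.

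The design gives the education to everyone:
- Abstract, Methods: "Both arms will receive usual care, which includes education about DD".
- Study Design and Setting: "Both arms of the study (control and intervention) will receive the standard of care detailed in Textbox 1". Textbox 1 lists the DD-specific education as part of that standard of care and says of the programme that it "is being piloted through this study".
- Training of Intervention Staff: the education "for participants in both arms of the study will be provided by designated medical assistants in the clinic".

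Patients are selected on the outcome scale. Textbox 2 requires at least moderate distress, "operationalized as a mean score of 2.0 or more on the 17-item diabetes distress scale". Under Measures and Data Collection, "DD will be assessed using the previously validated 17-item DDS", with measurements "at baseline (randomization), and at the third and sixth month postrandomization".

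The Data Analysis section compares mean change between the two arms, and the sample size rests on that between-arm difference alone. The abstract's objective does not list the education-alone question.

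**The concern.** A primary aim tells the reader which conclusion the trial is built to support. Here the only data on whether education is enough come from one arm followed over time, with no group that goes without education.

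Three things besides education can move that arm's mean: the other elements of usual care in Textbox 1 (quarterly visits, drug treatment, self-management support, depression referral), any time trend, and regression to the mean from enrolling people with high scores on the same scale. A fall from these sources could be read as proof that a newly developed programme works. Such a claim would appear to carry the authority of a randomised trial without resting on randomisation. An analysis plan cannot repair this, because the missing element is a comparator.

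**Working it through.** **1. The plan's own figure.** Inputs from Sample Size Determination: SD 0.89 at baseline and 0.81 at follow-up, correlation 0.5, difference 0.5, alpha 5% (taken as two-sided), power 80%, ratio 3:1, attrition 20%.

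- SD of change = √(0.89² + 0.81² − 2 × 0.5 × 0.89 × 0.81) = √0.7273 = 0.853.
- Smaller arm = (1 + 1/3) × (1.960 + 0.842)² × 0.7273 / 0.5² = 30.4, so 31 completers.
- 31 / 0.8 = 38.75, so 39 randomised; 3 × 39 = 117; total 156.
- Power with 31 and 93 completers: 80.7% at 0.5 and 92.4% at 0.6 (normal approximation).

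The stated 156 and both power statements reproduce. They concern only the comparison of coaching with education.

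**2. What each aim can draw on.**

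| Primary aim | Contrast needed | Contrast in the design |
|---|---|---|
| Coaching adds to education | Coaching plus education v education | Yes, randomised |
| Education alone is sufficient | Education v no education | None; control-arm change only |

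The article describes no run-in, historical control or external control.

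**3. How large regression to the mean could be.** Assumptions: the qualifying DDS is also the baseline; scores in the screened population are normal with the same mean μ and SD at both times; education has no effect. The documents do not give μ, so it is varied from 1.5 to 3.0.

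With c = (2.0 − μ)/SD and λ = φ(c)/(1 − Φ(c)), the expected fall is (1 − ρ) × SD × λ. With SD 0.89 and ρ 0.5:

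| Screened mean μ | Expected fall | As share of 0.5 |
|---|---|---|
| 1.5 | 0.53 | 106% |
| 2.0 | 0.36 | 71% |
| 2.5 | 0.21 | 43% |
| 3.0 | 0.11 | 22% |

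**4. What would count as significant.** With 93 control completers, SE = 0.853/√93 = 0.088. A two-sided 5% test of the control arm's change against zero would need a fall of about 0.18. Expected regression exceeds that for μ up to 2.5 but not at 3.0.

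**5. Sensitivity.**
- With ρ 0.7 and SD 0.89, the fall is 0.32 at μ 1.5 and 0.07 at μ 3.0.
- If SD 0.89 and ρ 0.5 describe enrolled rather than screened patients, the screened values can be solved from: enrolled SD = S√v and enrolled correlation = R√v/√(R²v + 1 − R²), where S and R are the screened SD and correlation, c and λ are computed with S, and v = 1 + cλ − λ². This gives S of 1.62 to 1.16 and R of 0.72 to 0.60, with an expected fall, (1 − R)Sλ, of 0.45 to 0.16 for μ 1.5 to 3.0.
- If a separate DDS is taken at randomisation, and correlations between occasions are equal, the expected fall from that score is about zero. Usual care and time trend would still be mixed with any education effect.

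**The case against.** The strongest reply is that the trial never proposes to test education on its own. The analysis and the power calculation are between-arm, no control-arm test or success rule for sufficiency is stated, and the abstract omits the aim. The two aims can be read as one question: is education enough, or does coaching add to it? That reading is possible and would make the randomised contrast the right evidence. But the Introduction sets the two out as separate primary aims. An added effect of coaching, or its absence, does not show whether education itself reduces distress.

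A reader might go further and infer that the control arm will, or very probably will, show a false education effect. The documents do not support that, for four reasons:
- The screened mean is not given. At 3.0 the expected fall is 0.11, and the chance of a significant result from regression alone is about 23%.
- SD 0.89 and correlation 0.5 are planning values for enrolled patients. Treating them as screened values implies an enrolled baseline SD of only 0.45 to 0.63 at screened means of 1.5 to 2.5.
- The article does not settle whether the qualifying score is the baseline. Screening is described as a clinic activity, baseline is placed at randomisation, and Figure 1 is not shown.
- Any probability of a significant before-after fall presupposes a test the plan does not specify.

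Nor does regression to the mean bias the coaching comparison, since it is expected equally in both randomised arms.

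**Conclusion.** The point holds as a mismatch between a stated primary aim and the design. It should be fixed, but it does not undermine the trial. The absence of a comparator follows from the article's text and needs no assumption.

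Regression to the mean is a secondary, conditional part. Roughly 0.1 to 0.5 points is plausible if the qualifying DDS is also the baseline, scores are roughly normal, SD is 0.89, correlation is 0.5 and the screened mean lies between 1.5 and 3.0. That could pass for an education effect. It matches the 0.5 points the plan calls clinically significant only near a screened mean of 1.5.

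**What to change.** Keep one primary aim: the effect of coaching added to education plus usual care. Move the education question to a descriptive objective. Report the control arm's change with its confidence interval, state that it includes usual care, time trend and regression to the mean, and make no claim of an education effect. State whether the DDS at randomisation is a separate measurement from the screening score; if it is, measure change from that score.

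The cost is a reworded aim, a sentence in the analysis section, and giving up a claim the design cannot support. Arms, sample size and data collection stay as they are. Keeping the aim as primary would instead require a comparator without the education.

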## Methods

### Study Design and Setting

A 2-arm, parallel RCT is being conducted among adults with diabetes who are not meeting glycemic targets (defined as HbA_1c_ ≥8.0), at an academic family medicine clinic in Houston, Texas. The overarching goal of the study is to use a pragmatic approach to assess the effectiveness of HC in addressing DD in real-world primary care settings, in which most diabetes care is coordinated and monitored. Therefore, participants randomized to the control group will receive the current standard of care for patients not meeting glycemic targets at the study clinic as summarized in Textbox 1.

Both arms of the study (control and intervention) will receive the standard of care detailed in Textbox 1. In addition, the intervention arm will receive 8 HC sessions to address DD. The HC sessions will be held biweekly in the first 3 months (6 sessions), followed by monthly sessions in the fourth and fifth month.

Standard of care for diabetes at the study site.Quarterly follow-up visits during which patients receive ongoing, comprehensive assessment and treatment. When patients with diabetes whose HbA_1c_ is 8.0 or above exceed a 4-month period without a visit, they are contacted to schedule a follow-up appointment.Pharmacologic treatment of diabetes and comorbiditiesBehavioral management—diabetes self-management education and support (DSMES), that covers lifestyle modification counseling (nutrition and physical activity), medication-taking behaviors, foot care, how to monitor blood glucose (especially for those on insulin), and how to administer insulin if on insulin. This ongoing DSMES is provided through different means as follows:Directly by primary care providersVia health education handouts in the form of printed materials and via an electronic patient portalBy referral to a registered dietitian located at the clinicReferral to an ophthalmology clinic for annual eye check-upPsychological management—as part of a newly developed quality improvement project, and in line with the 2018 American Diabetes Association’s Standards of Medical Care in Diabetes [10], the clinic has implemented psychological screening (depression and diabetes distress) for patients not meeting their glycemic targets (defined as HbA_1c_ ≥8.0). The plan of action is as follows:Patients who screen positive for depression (using the Patient Health Questionnaire) [17] will be referred to colocated mental health providers.A diabetes distress (DD)-specific education program has been developed for patients with DD and is being piloted through this study (Multimedia Appendix 1). This education program is oriented around the 4 domains of DD—regimen distress, emotional burden, interpersonal distress, and physician distress. Patients are provided feedback on DD screening results and are advised on ways to deal with the areas of greatest distress. Screening for DD is done using the 17-item DD scale (DDS17) [18].

### Description of the Coaching Intervention for Patients With Diabetes Distress

#### Coaching Approach

Even as HC is becoming more common in primary care, there is a wide and varied understanding of what constitutes HC [12]. For the purposes of this study, the authors use the term HC to refer to an intervention with a goal of facilitating health behavior change, conducted by a health care professional (eg, registered nurse, registered dietitian, medical assistant, clinical psychologist) who has additional training and certification as a health coach. Thus, interventions carried out by peers or lay people will not meet this standard. The authors align with the conceptualization of HC as articulated in the reviews by Olsen [12] and Wolever et al [13] and reflected in the following definition:

A patient-centered approach wherein patients at least partially determine their goals, use self-discovery or active learning processes together with content education to work toward their goals, and self-monitor behaviors to increase accountability, all within the context of an interpersonal relationship with a coach. The coach is a healthcare professional trained in behavior change theory, motivational strategies, and communication techniques, which are used to assist patients to develop intrinsic motivation and obtain skills to create sustainable change for improved health and well-being.
12

Interventions for alleviating DD need to address 2 issues: the first is helping the patient express his or her feelings about diabetes, and the second is to work with the patient to figure out what can be done to meet the patient’s needs [19]. Coaching techniques suitable for achieving the first objective include building a growth-promoting relationship with the client, establishing trust and rapport through the application of 3 core coaching skills, namely mindful listening, open-ended inquiry, and perceptive reflections [20], and helping clients handle negative emotions through an empathy protocol such as nonviolent communication [21]. To address the second objective of meeting the patient’s needs, the coach will help participants elicit self-motivation, build self-efficacy, and journey through a process of change to reach their desired goals, relying on techniques such as exploring and amplifying the best in the client through appreciative inquiry [22] and building self-efficacy through motivational interviewing [23].

The abovementioned techniques for addressing the 2 issues in DD provide the overall framework that the coach will work with to help participants address DD and overcome the underlying challenges contributing to their distress. Among these techniques, motivational interviewing is probably the best described and standardized, and it has been demonstrated to be effective in many settings [24-28].

A true HC approach recognizes that each patient is unique, focuses on meeting the needs of the patient, and emphasizes relationship development between the coach and client [12,13]. As each participant’s needs and values will be unique, the coach will tailor the intervention to the needs of each participant while staying within the overall coaching framework described above. This approach of not restricting the intervention to a rigid protocol is in keeping with the understanding that flexibility within the overall coaching paradigm is key to successful coach-client collaboration [12,13].

All coaching sessions will be delivered over the phone (ie, telecoaching) to minimize inconvenience, transportation time, and cost demands to participants. Telecoaching has been previously shown to be highly acceptable, low-cost, and effective in increasing autonomy and self-efficacy among adult patients with diabetes [29].

